### 2.8. Statistical Analysis

Categorical variables include pattern identification results diagnosed by the Korean medicine doctors and those obtained from questionnaires for pattern identification. These variables will be used for subgroup analyses and as outcomes for AI-based prediction models, facilitating comparisons of differentiation patterns based on specific diagnostic results and bio-signals.

The questionnaire results of the NDI, STAI, BDI-II, and EQ-5D will be treated as numerical variables. The normality of the questionnaire results will be assessed to determine suitable statistical tests. Depending on normality, statistical tests like *t*-tests, analysis of variance, or non-parametric tests will be used to compare groups. Subgroup analyses will compare bio-signals between different diagnostic patterns. Correlation analyses will explore the relationships between the questionnaire results and categorical variables, while mediation and moderation analyses will assess potential factors that mediate or moderate the effects among the variables.

Bio-signal data, including fNIRS, SCR, ECG, and pulse waves, will be processed as both numerical and time-series data. First, basic preprocessing steps will be applied to the bio-signal data. For fNIRS data, preprocessing will be conducted using NIRSIT QUEST software (NIRSIT; OBELAB Inc., Seoul, Republic of Korea). The preprocessing steps will include the rejection of channels with an intensity lower than 30 AU, motion artifact correction using temporal derivative distribution repair filtering for optical density data, and the correlation-based signal improvement method for hemoglobin data. Additionally, an oxygen saturation threshold will be set at 5%, and band-pass filtering will be applied at a range of 0.01–0.2 Hz. Resting-state levels of oxyhemoglobin (HbO), deoxyhemoglobin (HbR), and total hemoglobin (HbT; HbO + HbR) will be averaged over a 2 min period across various Brodmann areas of the frontal cortex, including the dorsolateral prefrontal cortex (DLPFC), frontopolar prefrontal cortex (FPC), orbitofrontal cortex (OFC), and ventrolateral prefrontal cortex (VLPFC). The connectivity patterns among these regions will then be analyzed. SCR and ECG data will be analyzed using the “NeuroKit2” package in Python [38]. For SCR data, preprocessing steps will include low-pass filtering to remove high-frequency noise, artifact correction to address distortions, and baseline correction to isolate phasic responses. SCR peaks will be then identified and normalized. The phasic and tonic activity, as well as the amplitude and height of signals, will be extracted. For ECG data, preprocessing steps will include using NeuroKit2 for signal filtering to remove noise, artifact correction to address any distortions, and baseline correction to stabilize the signal. R-peaks will be then detected and intervals such as RR intervals will be computed for further analysis. Heart rate and HRV statistical and spectral analyses will be conducted using the standard methods. Pulse wave signals will be preprocessed by removing noise and deleting signals from sensors where measurement errors have occurred based on visual inspection and then processed into various time-related and frequency-related parameters, such as H1, H3, and H4.

For time-series bio-signals, various machine learning techniques have been shown to be effective in identifying spatiotemporal patterns for predictive and diagnostic tasks [39]. For single-channel signals, such as ECG or SCR, we plan to extract meaningful features that represent the physiological state or detect abnormalities using machine learning models, such as the random forest model. These features include traditional metrics (e.g., R-peak detection and morphological analysis) as well as advanced decomposition techniques (e.g., wavelet transforms and empirical mode decomposition) that facilitate the extraction of time–frequency domain characteristics to capture subtle and non-stationary signal behaviors [40]. Furthermore, deep learning-based methods, including 1D convolutional neural networks (CNNs) and transformer architectures, will be employed for automated and robust representation learning directly from raw signals.

For multi-channel signals, such as fNIRS or pulse wave data, we will utilize both linear and non-linear analytical methods to evaluate signal rhythms and variability. Recently introduced approaches (e.g., network analysis and attention-based models) allow for the modeling of long-term dependencies, revealing spatiotemporal patterns that traditional methods often fail to detect [41,42]. Graph-based models, such as graph neural networks and graph convolutional networks, show potential for analyzing inter-channel connectivity and exploring the functional relationships among multiple bio-signal sources [43]. By leveraging classical connectivity metrics, such as phase-locking values or mutual information, we expect these integrated approaches to yield more accurate and interpretable results.

To address potential confounding variables, we have identified key confounders such as variability in bio-signal measurements, subjectivity in diagnoses, and multi-collinearity among bio-signals. We will use multivariate regression and regularization techniques like Least Absolute Shrinkage and Selection Operator or ridge regression to handle multi-collinearity and apply principal component analysis for dimensionality reduction. Additionally, to ensure our models are based mainly on bio-signals, we will exclude questionnaire scores that strongly correlate with specific patterns. This approach helps maintain model robustness and aligns with our primary study objective.

Additionally, we will investigate local and relative differences in brain activity through amplitude and frequency power analysis. Frequency-domain techniques (e.g., Fast Fourier Transform (FFT), Short Time Fourier Transform (STFT), and wavelet transforms) can be applied to extract spectral features from bio-signals, capturing power distributions across key frequency bands [44]. Recent hybrid approaches transform time-frequency representations into image-like inputs, enabling the use of CNN-based models to automatically discern frequency-related patterns. These methods can be used to enhance the sensitivity of diagnostic tools, particularly for complex and non-stationary bio-signals [45]. The significance and validity of the model will be assessed based on the classification accuracy and the area under the receiver operating characteristic (ROC) curve. These metrics will be obtained through bootstrapping and cross-validation methods and tested against a chance level (0.5, 0.33, or 0.17, depending on the prediction outcomes) using a *t*-test with a significance level of *p* < 0.05.

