The second visit will involve a review of medication use and menstrual cycle details for female participants. The vital signs will be measured again, and participants will complete a series of questionnaires, including the Standard Tool for Pattern Identification of FD [2], Cold–Heat Pattern Questionnaire [26], Deficiency–Excess Pattern Questionnaire [27,28], Phlegm Pattern Questionnaire [29], Food Retention Questionnaire [30], Spleen Qi Deficiency Questionnaire [31,32], Stomach Qi Deficiency Questionnaire [33], Nepean Dyspepsia Index (NDI) [34], State-Trait Anxiety Inventory (STAI) [35], Beck Depression Inventory-II (BDI-II) [36], and the EeroQol-5-Dimension (EQ-5D) [37]. Participants may opt out of answering any questions they find uncomfortable. The Standard Tool for Pattern Identification of FD questionnaire comprises 45 items that categorize FD symptoms into six types: liver–stomach disharmony, dampness and heat in the spleen and stomach, spleen and stomach deficiency and cold, tangled cold and heat, food retention disorder, and insufficiency of stomach yin. This questionnaire demonstrates high reliability, indicated by its internal consistency, and a moderate level of validity, based on correlation analyses between the FD patterns identified by the tool, the Rome IV subtypes, and other dyspepsia-related questionnaires [2]. In addition, the Cold–Heat Pattern Questionnaire [26], Deficiency–Excess Pattern Questionnaire [27,28], Phlegm Pattern Questionnaire [29], Food Retention Questionnaire [30], Spleen Qi Deficiency Questionnaire [31,32], and Stomach Qi Deficiency Questionnaire [33] have been developed as pattern identification tools. These patterns are recognized as being significantly related to FD and the tools have been validated for both reliability and validity.

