### 2.7. Data Collection

Pattern identification will be conducted by licensed Korean medicine doctors via questioning, tongue diagnosis, pulse diagnosis, and abdominal diagnosis. This assessment determines deficiency–excess, cold–heat, and the presence of phlegm or food stagnation, as well as six primary FD differentiation patterns (spleen and stomach deficiency–cold, spleen Qi deficiency, liver–stomach disharmony, food stagnation, spleen deficiency with damp–heat, mixed cold and heat).

Bio-signal measurements will be conducted during the second visit or during the first visit only if the screening procedures confirm that the participants meet the inclusion criteria. Prefrontal cortex activity will be measured using a headband-type fNIRS device (NIRSIT; OBELAB Inc., Seoul, Republic of Korea). SCR, ECG, and pulse wave signals will be recorded with electrodes attached to the fingers, wrist, and chest, connected to the Biopac MP160 system (BIOPAC Systems Inc., Goleta, CA, USA). Radial artery pulse waves will also be measured using the DMP-LIFE PLUS pulse analyzer (DAEYOMEDI Co., Ltd., Ansan, Republic of Korea). These measurements will be conducted with the participants in supine position for two minutes. To maintain objectivity, the researcher measuring biometric signals will be different from the doctors diagnosing the patients with FD. Additionally, the diagnosis and pattern identification results will be blinded to both the researcher and the participants. Throughout the measurements, participants will be monitored thoroughly for any discomfort or adverse events.

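### Doctor-assigned and questionnaire-derived patterns are all prediction outcomes with none named primary, and each model is judged at an unadjusted p < 0.05, which inflates the chance of a falsely valid model

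*Protocol article*

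**What the plan says.** All references are to the protocol article.

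- **Label sources.** Section 2.8: "Categorical variables include pattern identification results diagnosed by the Korean medicine doctors and those obtained from questionnaires for pattern identification". The next sentence gives both sources the role of model outcome and of subgroup variable. Neither is ranked.
- **Doctor labels.** Section 2.7 has the doctors decide deficiency–excess, cold–heat, phlegm and food stagnation, and assign one of six patterns: "spleen and stomach deficiency–cold, spleen Qi deficiency, liver–stomach disharmony, food stagnation, spleen deficiency with damp–heat, mixed cold and heat".
- **Questionnaire labels.** Section 2.6 lists seven pattern tools. One, the Standard Tool, has its own six types, ending with "tangled cold and heat, food retention disorder, and insufficiency of stomach yin".
- **Criterion.** Section 2.8 says the significance and validity of the model will be "assessed based on the classification accuracy and the area under the receiver operating characteristic (ROC) curve". It continues: "These metrics will be obtained through bootstrapping and cross-validation methods". The values are then "tested against a chance level (0.5, 0.33, or 0.17, depending on the prediction outcomes") by a t-test "with a significance level of *p* < 0.05".
- **Models.** Random forest is named for single-channel signals, and "deep learning-based methods, including 1D convolutional neural networks (CNNs) and transformer architectures, will be employed" as well. LASSO and ridge are named for collinearity. Graph-based models are only said to show potential.
- **Sample size.** Section 2.3 asks for at least 50 samples per category and sets N at 100.

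**The concern.** The rule for calling a model valid is written down, carries no adjustment, and is attached to no single outcome. The three chance levels show that two-, three- and six-category outcomes are all meant to be tested. With up to a dozen labels open to the same 5% rule, a study with no signal at all has a substantial chance of reporting a valid model for one of them.

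The target is also unclear. The study aims to help standardise pattern diagnosis, but it has two six-pattern systems that are not the same. A reader told that a six-class model beats 0.17 cannot know what was predicted unless the source of the label is fixed in advance.

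**Working it through.** **1. The plan's own figure.** N = 50 × number of categories. Two categories: 50 × 2 = 100, which matches. Three: 150. Six: 300. So N = 100 meets its own basis only for a two-category label split about evenly. With six categories the average is 100/6 = 16.7 patients each.

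**2. Number of outcomes.** Section 2.7 gives 4 single labels + 1 six-pattern label = 5. Section 2.6 gives 7 tools. Total 5 + 7 = 12. That each is modelled once is an assumption; the article gives no count.

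**3. Independent tests, each with a true 5% level.** P(at least one false positive) = 1 − 0.95^k.

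- Doctor labels only, k = 5: 1 − 0.95^5 = 22.6%
- All labels, k = 12: 1 − 0.95^12 = 46.0%

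**4. Correlated tests.** The labels overlap in content, so independence gives an upper figure. Test statistics were simulated as Z_k = √ρ·G + √(1 − ρ)·E_k (G a shared and E_k a separate standard normal), with one-sided 5% tests and 100,000 runs. The ρ values are assumptions.

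- k = 12, ρ = 0.3: 34%
- k = 12, ρ = 0.5: 27%

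**5. Sidedness.** The article does not state it. If the test is two-sided and only results above chance count, each test spends 2.5%: 1 − 0.975^12 = 26.2% with independence, and 20% at ρ = 0.3.

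**6. Several models per label.** The number is an assumption. With correlation 0.3–0.5 between labels and 0.5–0.8 between models on one label, one-sided 5%:

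| Models per label (12 labels) | Chance of at least one false positive |
|---|---|
| 1 | 27–34% |
| 3 | 39–55% |
| 6 | 47–68% |

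**7. The two six-pattern lists.**

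| Doctors (section 2.7) | Standard Tool (section 2.6) |
|---|---|
| Liver–stomach disharmony | Same |
| Spleen and stomach deficiency–cold | Same apart from wording |
| Food stagnation | Food retention |
| Mixed cold and heat | Tangled cold and heat |
| Damp–heat, with spleen deficiency | Damp–heat, no mention of deficiency |
| Spleen Qi deficiency | None |
| None | Insufficiency of stomach yin |

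Four categories correspond, one pair is worded differently, and each list has one category that the other lacks.

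**8. Does a single test hold 5%?** Steps 3 to 6 take this for granted. A null simulation checked it: n = 100, balanced classes, ten noise features, a ridge linear classifier, 600 runs, and a two-sided t-test at 0.05 counted only above chance (nominal 2.5%). The false-positive rate was about 6% with one 10-fold cross-validation, 33% with ten repeats of it and 29% with 100 bootstraps. The replicates reuse the same patients, so the t-test treats dependent values as independent. The classifier, the features and the numbers of repeats are assumptions.

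**The case against.** **The article is condensed.** A ranking of outcomes, a multiplicity rule and nested cross-validation may sit in a full protocol or SAP that is not shown. This stands as far as pure silence goes. It does not remove what section 2.8 states: two outcome sources and a validity rule at an unadjusted 0.05.

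**The sources may not be equal.** The abstract pairs bio-signals with the doctors' diagnoses, section 2.7 calls the doctors' six patterns primary, and section 2.8 treats questionnaire scores as candidate inputs, some to be excluded. These are hints that the doctors' label is the reference. None assigns that role, and section 2.8 still makes both sources outcomes.

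**Stronger readings that the text does not support.**

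- A reader might infer that every label is crossed with every model family. No such crossing is stated. The families are tied to signal types, and graph models are not committed to.
- A reader might infer that the two six-pattern lists will be merged into one outcome. Nothing pools them, and two instruments may have different categories. A separate Spleen Qi Deficiency Questionnaire also exists. The point is only that the two lists are not interchangeable.
- A reader might infer that models will be chosen and evaluated on the same folds. The article does not say so.

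**The study is exploratory.** The discussion calls it an initial step, so strict error control can be debated. But the plan itself uses a p-value to declare a model valid, and that rule should mean what it says.

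**Conclusion.** The concern holds in limited form. As written, the plan applies an unadjusted 5% validity rule to several unranked outcomes from two sources. With 12 labels modelled once by valid tests, the chance of at least one false positive is up to 46% if independent and about 27–34% at correlations of 0.5 to 0.3. It is lower if only the upper tail of a two-sided test counts, and higher if several models are tried. The label count, the correlations and the number of models are assumptions.

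A reader might infer that a significant model is almost certain, for example by counting accuracy and AUC as separate tests: 12 × 2 = 24 and 1 − 0.95^24 = 71%. That is not supported. Both metrics come from the same predictions and cannot be treated as independent, and the figures at the nominal level with one model per label stay below one half.

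The mismatch of the two lists is a fact of the text. It means that a six-class result must be tied to its label source.

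**What to change.** 1. Name one primary outcome: a doctor-assigned label with two categories, the only kind for which 50 per category gives N = 100, and then only if the split is about even. The 0.33 chance level implies that some labels have three categories, so state the number of categories for each label. Make AUC the primary metric.
2. Choose the model and its settings in the inner loop of nested cross-validation, so that the outer folds only evaluate.
3. Replace the t-test on resampled values with a test that is valid for them, such as permutation of the labels with the whole pipeline rerun. This comes before any adjustment: Holm controls the error only if each single test holds its level.
4. Holm-adjust the other four doctor labels; the smallest p-value is then compared with 0.05/4 = 0.0125.
5. Report questionnaire-derived labels as secondary and separately from the doctors' labels. Give kappa between the two sources on the shared categories. Decide in advance whether the damp–heat pair counts as shared, and state how many patients fall outside.

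The cost is wording and more computing time, mostly for permutation around nested cross-validation. No patients or procedures are added. Fewer outcomes can be claimed as confirmed.

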
Pulse wave signals, generated by radial artery pulsations, reflect hemodynamic changes. Technological advancements have led to the development of pulse diagnostic devices that analyze variables, such as power spectrum, signal amplitude, frequency, regularity, and volume. In particular, the measurement of pulse signals and the analysis of pulse wave signals are increasingly used for the diagnosis and monitoring of cardiovascular and systemic diseases like diabetes, thereby expanding their clinical applications. Recent studies have explored artificial intelligence (AI) techniques to analyze pulse wave time-series data, aiming to extract clinically meaningful information and provide objective interpretations of traditional pulse patterns with significant prediction accuracy [5,6,7,8].

Functional dyspepsia (FD) is a relapsing and remitting chronic gastrointestinal disorder characterized by postprandial fullness, early satiation, and epigastric pain or burning not associated with defecation, which are not fully explained by other medical conditions [9]. Patients with FD exhibit altered brain activity in regions including the prefrontal cortex, somatosensory cortex, insula, anterior cingulate cortex, amygdala, and hippocampus [10,11,12]. Additionally, autonomic nervous system activity is an important diagnostic factor in gastrointestinal disorders, as imbalanced sympatho-vagal and autonomic responses are associated with alterations in gastrointestinal functions and symptoms [13]. For example, patients with FD showed a significantly increased skin conductance response (SCR) in response to external stressful stimuli compared to healthy controls [14], and patients diagnosed with both postprandial distress syndrome and epigastric pain syndrome showed a significantly greater low frequency/high frequency ratio measured by heart rate variability (HRV) after a drink test [15].

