### 2.6. Study Procedures

The study is organized into two in-person visits. The initial phone screening will be conducted to gather information on recent upper endoscopy and blood test results, symptoms and diagnosis of functional dyspepsia, medical history, medication use, alarm symptoms, and the inclusion and exclusion criteria. Participants deemed eligible for study participation during the phone screening will be invited to attend the first visit, which is dedicated to screening the participants, while the second visit will focus on bio-signal measurements.

During the first visit, participants will be provided with a detailed explanation of the study, and written informed consent will be obtained. Demographic data, medical and surgical history, and current medication use will be collected. Vital signs, including blood pressure, heart rate, and body temperature, will be measured, alongside anthropometric data, such as height and weight. Blood tests and an electrocardiogram (ECG) will be conducted unless results from the past year are available. FD symptoms will be assessed using the Visual Analog Scale (VAS), and a diagnosis will be confirmed through the Rome IV criteria. Eligibility will be determined based on the aforementioned inclusion and exclusion criteria.

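### The confounder list names no patient characteristic, and the planned bio-signal comparisons between patterns state no adjustment for age or sex

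*Protocol article*

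**What the plan says.** Section 2.8 (Statistical Analysis) first treats the questionnaire scores as numerical and makes the choice of test depend on their normality: "Depending on normality, statistical tests like *t*-tests, analysis of variance, or non-parametric tests will be used to compare groups". The next sentence reads "Subgroup analyses will compare bio-signals between different diagnostic patterns". It names no test or model of its own and no covariate. Mediation and moderation analyses follow, without naming their variables.

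Later in section 2.8 the authors take up confounding directly. They say they have identified "key confounders such as variability in bio-signal measurements, subjectivity in diagnoses, and multi-collinearity among bio-signals". The remedies given are multivariate regression with LASSO or ridge penalties, whose stated purpose is multi-collinearity, and principal component analysis for dimension reduction.

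Patient characteristics are collected. Section 2.6 lists demographic data and "anthropometric data, such as height and weight" at the first visit, and "a review of medication use and menstrual cycle details for female participants" at the second. Section 2.4.1 admits adults aged 19 to 65. No analysis in section 2.8 is said to use age, sex, body size or menstrual details.

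**The concern.** Pattern groups are formed by diagnosis, not by randomisation. The Introduction says that a pattern is identified from overall health, including lifestyle and constitution, so the groups may well differ in who is in them. The protocol accepts that patient-level factors move bio-signals: section 2.4.2 excludes people with certain diseases or medications for that reason. Yet the confounder list holds only measurement variability, label subjectivity and collinearity. The last of these is a relation among predictors and does not confound a comparison of one signal between patterns.

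These comparisons are where a report would say that one pattern has, for example, a higher LF/HF ratio or a different pulse amplitude. If the groups differ in age or sex, and the signal varies with age or sex, that statement may describe the demographic difference. This is separate from the test of the prediction model against chance, also in section 2.8. Repairing that test would not touch these comparisons.

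**Working it through.** **Inputs from the protocol article.** The sample size is 100, from a minimum of 50 per category (section 2.3). 50 × 2 = 100 reproduces the stated total for two categories, which is why the main illustration uses two groups of 50. With six patterns, 100/6 is about 17 per group. Ages run from 19 to 65 (section 2.4.1). The 0.05 level is stated only for the test of the model against chance; it is carried over here, two-sided, as an assumption.

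**Assumed inputs.** The documents give no age gap between patterns, no age–signal correlation, no sex split and no sex effect. If ages are roughly uniform, their SD is (65 − 19)/√12 = 13.3 years, so a gap of 0.5 SD is about 6.6 years. The correlation r between age and signal is taken as 0.3 to 0.5. There is no true pattern effect given age and sex.

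**Closed form, two groups of 50, no adjustment.**
- Spurious difference = r × gap: 0.3 × 0.5 = 0.15 SD; 0.5 × 0.5 = 0.25 SD.
- Standard error = √(1/50 + 1/50) = 0.20 SD.
- Ratio λ = 0.15/0.20 = 0.75; 0.25/0.20 = 1.25.
- Rejection probability ≈ Φ(λ − 1.96) + Φ(−λ − 1.96): 0.113 + 0.003 = 0.116; 0.239 + 0.001 = 0.240.

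**Simulation.** Two set-ups were run, with 6,000 and 4,000 replicates per setting. Each compared the unadjusted test with a linear model containing the covariates. Where both covered a setting, both results are shown. Groups are of 50 unless stated.

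| Assumed imbalance | Unadjusted | Adjusted |
|---|---|---|
| None | 4.5% | 4.4% |
| Age gap 0.5 SD, r = 0.3 | 11.0%, 11.9% | about 5% |
| Age gap 0.5 SD, r = 0.5 | 23.6%, 24.9% | about 5% |
| Women 60% vs 80%, sex effect 0.5 SD | 7.4% | 4.5% |
| Women 50% vs 90%, sex effect 0.5 SD | 17.1% | 4.7% |
| Women 60% vs 80% (0.5 SD) plus age gap 0.5 SD (slope 0.4) | 31.3% | 4.8% |
| The same, 17 per group | 13.2% | 5.1% |
| Six groups, mean ages spread over 1.0 SD, r = 0.3 to 0.5 | 10.0% to 20.4% | about 5% |

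The mildest imbalances gave about 7% unadjusted. The most extreme (women 50% vs 90%, age gap 0.5 SD with slope 0.5) gave 58.8%, against 5.7% adjusted. The closed form agrees with the simulations for the two age-gap rows.

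**Precision.** With no imbalance, adjusting for age raised power for a 0.5 SD difference from about 69% to 73% (r = 0.3) or 80% (r = 0.5). The corresponding gain in information is 1/(1 − r²) − 1, that is 10% and 33%.

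**The case against.** The strongest reply is that the article never says the comparisons are unadjusted. The test list follows a normality check on questionnaire scores, it is open-ended, and the bio-signal sentence names no method. A covariate set may stand in an analysis plan that is not shown. This much is right: a reader may infer that the protocol fixes unadjusted bio-signal tests, but that is only the natural reading of "analysis of variance, or non-parametric tests will be used to compare groups". A missing covariate list alone would be no finding. What stands against the reply is that section 2.8 goes on to say what the key confounders are. That list is illustrative, not closed, but every item on it is something other than a patient characteristic, and the regression beside it serves another purpose. The mediation and moderation analyses name no variables and answer a different question.

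Second, raw and adjusted comparisons answer different questions. A raw difference correctly describes how signals differ between patients with different patterns, and a false positive exists here only for the question conditional on age and sex. That is fair, and it is why both should be reported. It also weighs against obligatory adjustment for body size, since constitution may be part of what a pattern describes.

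Third, a reader might infer that Rome IV status or subtype is a further confounder. The Introduction reports that "patients diagnosed with both postprandial distress syndrome and epigastric pain syndrome showed a significantly greater low frequency/high frequency ratio", and section 2.6 says the pattern tool was validated partly through "correlation analyses between the FD patterns identified by the tool, the Rome IV subtypes". The documents do not support this as a finding. Every participant must meet Rome IV, so status cannot differ between patterns, and nothing says that subtype is recorded. The LF/HF result came after a drink test, whereas section 2.7 plans two-minute supine recordings and mentions no such test.

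**Conclusion.** The point holds in a limited form. The protocol article plans bio-signal comparisons between non-randomised groups, states no covariates for them, and treats confounding without naming any patient characteristic. An age or sex difference could therefore be taken for a pattern signature.

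The direction follows from covariate effect times imbalance. The size cannot be taken from the documents. The 11–25% against about 5% rests on the assumed 0.5 SD age gap, r of 0.3 to 0.5 and groups of 50, with no pattern effect given age and sex. It shows what could happen and does not show that the study's comparisons will be biased. If the patterns turn out balanced on age and sex, the adjustment brings only some precision. This is a cheap improvement, not a flaw that undermines the study.

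**What to change.** In the confounding paragraph of section 2.8, add age and sex to the named confounders. For the comparison of bio-signals between patterns, specify a linear model with pattern as the factor and age (continuous) and sex as fixed covariates. Use robust standard errors or a rank-based version if residuals are not normal. Report adjusted differences with 95% intervals beside the raw group means.

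BMI, from the height and weight already collected, and menstrual phase in women may be added as sensitivity analyses, with a sentence saying that body constitution may be part of what the pattern describes. Leave Rome IV status and subtype out.

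The cost is a few lines of text and code, two degrees of freedom for the main covariates, and simple handling of any missing values. Age and sex are not itemised under demographic data, but age is an eligibility criterion and female participants are identified at the second visit, so no new visits, patients or measurements are needed.
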